## Methods: participants, interventions, and outcomes

### Study setting {9}

All aspects of the study will take place in the county of Los Angeles, CA, in the USA. The implementation of smoking services will be delivered in eighteen outpatient clinics, eleven from LACDHS operated outpatient primary care clinics and seven from LACDMH-operated community mental health clinics. As part of the study, fifteen of the eighteen clinics will provide smoking cessation services and two clinics will continue to offer treatment as usual, without enhanced smoking cessation services. Randomization will be used to determine which clinics will provide smoking cessation services. Participating outpatient clinics from LACDHS are (1) Martin Luther King, Jr. Outpatient Center (2); LAC + USC Medical Center (3); Edward R. Roybal Comprehensive Health Center (4); Harbor-UCLA Medical Center – General Internal Medicine (5); Harbor-UCLA Medical Center – Family Medicine (6); Mid Valley Comprehensive Health Center (7); Long Beach Comprehensive Health Center (8); High Desert Regional Health Center (9); Hubert H. Humphrey Comprehensive Health Center (10); Olive View – UCLA Medical Center; and (11) H. Claude Hudson Comprehensive Health Center. Participating outpatient clinics from LACDMH are (1) East San Gabriel Valley Health Center (2); Harbor – UCLA Mental Health Center (3); South Bay Mental Health Center (4); West Central Family Mental Health Center (5); West Valley Mental Health Center (6); Arcadia MHC; and (7) American Indian Counseling Center.

### Eligibility criteria {10}

Inclusion criteria for participants are as follows: (1) be 18 years old or older, (2) smoke three or more cigarettes or cigars per day, (3) have thought about stopping smoking, and (4) be enrolled in care at either LACDHS and/or LACDMH. Participants who use only electronic cigarettes, hookah, or other types of tobacco/nicotine will not be allowed in the study if they do not meet all inclusion criteria. Cigarette and cigar smokers who also use electronic cigarettes, hookah, or other types of tobacco/nicotine will be allowed in the study.

Exclusion criteria for participants are as follows: (1) under 18 years, (2) smoke less than three cigarettes or cigars per day, (3) not interested in stopping cigarette smoking, and (4) not enrolled in care at either LACDHS and/or LACDMH.

Based on our preliminary data and analysis, a significant number of dropouts are anticipated. An estimated 50% of enrolled participants will drop out. Since this is a pragmatic real-world trial, we accept the risk of a significant dropout rate. Furthermore, given that this is an implementation trial, study participants can continue to participate in the research assessments even if they do not participate in clinical services. A patient is considered a dropout if they report no longer wanting to participate in the research assessments or cannot be reached to complete research assessments.

### Who will take informed consent? {26a}

At the first interview and prior to conducting any research-related procedures, the clinical coordinator will discuss the written informed consent and outline the study procedures. Once the participant has asked questions and has a clear understanding of the study, the participant will sign the consent form and will be enrolled into the study.

### Additional consent provisions for collection and use of participant data and biological specimens {26b}

Not applicable as no additional participant data and biological specimens were collected as part of this trial.

### Interventions

#### Explanation for the choice of comparators {6b}

This is a cluster-randomized comparative effectiveness trial that compares intervention clinics offering smoking cessation group counseling and medication management integrated into primary care and community mental health clinics with TAU clinics offering information about the CA Smoker’s Helpline and informal provider counseling.

#### Intervention description {11a}

Each clinical site in LACDHS is part of a cluster, and there will be a 5:1 ratio in the assignment of both LACDHS and LACDMH clinics assigned to the intervention as compared with TAU. The smoking cessation intervention will be a program embedded in the participating clinics and will include (1) a weekly 60–75-min CBT smoking cessation counseling group which will be led by facilitators that have been trained through the Kick Ash program and may be a nurse, pharmacist, clinician, SUD counselor, behavioral health clinician, or counselor and (2) smoking cessation medication that will be prescribed by a psychiatrist, pharmacist, or primary care doctor licensed clinician. Participants will be offered 6 weekly consecutive groups focusing on gaining necessary skills to aid in the decrease or total cessation of smoking behaviors. Those attending the groups will gain alternative coping strategies, relapse prevention strategies, and tools and resources to assist with reaching smoking cessation. Regarding the counseling group, participants will be able to repeat the groups willingly as needed until total smoking cessation is obtained. Smoking cessation medications will include varenicline (Chantix), bupropion (Zyban), nicotine patches, gum, and lozenges. Participants prescribed varenicline will be prescribed 0.5 mg of varenicline once daily for 3 days, then 0.5 mg twice daily for the next 4 days, then 1 mg twice daily thereafter. Those prescribed bupropion (Zyban) SR 150mg will be offered and, if accepted, prescribed once daily for 1 week, followed by bupropion SR 300 mg once daily thereafter. Participants prescribed NRT will be prescribed the standard prescription for nicotine NRT which includes a transdermal patch at a dose that approximates their current average mg of nicotine intake from tobacco products. Nicotine gums or lozenges (in either 2 mg or 4 mg strength) will also be offered and can be used as needed when experiencing cravings to smoke. TAU offers information about the California Smoker’s Helpline and usual provider and clinician counseling. Participants in TAU will be asked at each data collection point (baseline and 3, 6, and 12 months) about any smoking cessation services received including prescribed and over-the-counter smoking cessation medication.

#### Criteria for discontinuing or modifying allocated interventions {11b}

The clinician or pharmacist will discuss with participants in detail the individual side effects associated with the smoking cessation medication to help the participant decide whether or not to take the medication. During this time, participants will provide the clinician or pharmacist with an accurate smoking and medical history to ensure the prescribed medication is safe for them. At each in-person study interview, the researcher will complete brief medical and mental health assessments. To note, in-person study interviews shifted to telephone interviews in response to COVID-19. Participants who experience any side effects can choose to meet with their healthcare provider to help them resolve the side effects by either discontinuing medication, modifying medication dosage, or other responses left to the discretion of the healthcare provider.

#### Strategies to improve adherence to interventions {11c}

To assist with adherence to intervention protocols, participants will be offered medications using a shared decision framework. Shared decision-making is an established medical practice where patients are invited to participate in selecting the treatment strategy that they would like to obtain [11, 12]. This has been associated with improved adherence to medication treatments. Participants will choose their own preferred treatment, pending any contraindications, during the 15-min medication management visit with a prescribing clinician. The shared decision-making medication protocol will permit flexible prescribing, such that participants can establish a quit date further than a week from initiation of smoking cessation medication. Additionally, participants can continue medication usage even if they continue actively smoking, provided that the clinician identifies ongoing clinical benefits to the smoking cessation medication treatments. To further assist with interview adherence, interviews will take place at the participant’s primary care clinic or the site they usually obtain county-provided services. Participants who are assigned to clinics that provide smoking cessation services will also be asked about the frequency of their participation in the smoking cessation services during the 12-month period.

### Relevant concomitant care permitted or prohibited during the trial {11d}

Concomitant medications that make it unsafe for a participant to be prescribed smoking cessation medication will be decided by the participant’s healthcare provider. All other concomitant care will be allowed.

### Provisions for post-trial care {30}

There are no provisions for ancillary and post-trial care. As the risks of the study are minimal, there are no plans to compensate those who suffer harm from trial participation. If a participant experiences an adverse event to the medical care received at a county site, they will be instructed to follow up with their healthcare provider.

### Outcomes {12}

The primary outcome of the study is higher rates of smoking cessation in the intervention sites as compared with matched LAC-operated setting non-intervention sites. Exploratory analysis will consider intervention effects on the smoking rate, such as smoking reductions. To measure rates of smoking cessation, study participants will complete two objective measures collected at four time points at 3-month intervals within a 12-month period. Analysis will be at each time point compared to baseline. The objective measures include a carbon monoxide breathalyzer (piCO+Smokerlyzer) and a urinary rapid dipstick cotinine test (NicCheck) before March 2020. However, these measures were temporarily discontinued in response to COVID-19 when data collection shifted from in-person to telephone collection.

The study will evaluate the (1) penetrance of smoking cessation medications and counseling services, at intervention and non-intervention sites and between mental health and primary care clinics; (2) self-reported cigarette use, smoking urges, number of quit attempts, changes in self-reported anxiety, stress, quality of life, and participant satisfaction; (3) and the dose effect of medication and counseling services on smoking cessation.

### Participant timeline {13}

The study design begins with implementation and delivery of the smoking cessation services, followed by healthcare staff surveys, study participant recruitment by the healthcare staff, enrollment into the study and smoking cessation services navigation by the research team for participants enrolled in clinics that will provide smoking cessation services, and participant follow-ups administered by the research team. See Fig. 1 for the study flowchart.

**Fig. 1 Fig1:**
[figure not shown]
Flow diagram illustrating participant’s timeline through the trial

### Sample size {14}

Prior to the beginning of the study, a formal power analysis was done. The plan is to enroll 1000 smokers in 14 clinical sites where specialty tobacco use disorder services (STUDS) are being offered and 200 smokers in 3 clinics in the TAU clinical sites and expect a dropout rate of 50%. Thus, a cluster-randomized study design was envisioned. If we assume that the intervention sites achieve a 25% success rate at achieving abstinence and the TAU group a 5% success rate, then with a reasonably sized intra-cluster correlation coefficient of 0.05, the power to detect a difference in success rate is 99.4%. This assumes a two-sided test of proportions (using a large sample approximation and the corresponding cluster adjustment) with a significance level of 5%.

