## Assignment of interventions: allocation

### Sequence generation {16a}

Block randomization will be by cluster using the program calculator.net. Each clinical site is a cluster, and there will be a 5:1 ratio in the assignment of *both* LACDHS and LACDMH clinics assigned to the intervention arm (offering STUDS) as compared with the TAU arm. A total of 18 study sites will be randomized on a 5:1 intervention to TAU ratio basis, with three TAU sites and fifteen intervention sites split as follows: 11 primary care clinics (9 intervention, 2 TAU) and 7 mental health clinics (6 interventions, 1 TAU).

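### The 99.4% power comes from a large-sample test that ignores having only three TAU clinics; small-cluster tests give about 81–93%, and the clinic counts disagree

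*Protocol article*

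**What the plan says.** Sample size {14} plans on two arms: "The plan is to enroll 1000 smokers in 14 clinical sites" offering the specialty service, and "200 smokers in 3 clinics in the TAU clinical sites and expect a dropout rate of 50" per cent. It assumes that "intervention sites achieve a 25% success rate at achieving abstinence and the TAU group a 5% success rate", takes "a reasonably sized intra-cluster correlation coefficient of 0.05", and concludes that "the power to detect a difference in success rate is 99.4" per cent. On method it adds: "This assumes a two-sided test of proportions (using a large sample approximation and the corresponding cluster adjustment) with a significance level of 5" per cent.

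The number of randomised clinics appears in three places:

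- Sample size {14}: 14 + 3 = 17.
- Study setting {9}: "fifteen of the eighteen clinics will provide smoking cessation services and two clinics will continue to offer treatment as usual", that is 15 + 2 = 17 of 18.
- Sequence generation {16a}: "with three TAU sites and fifteen intervention sites split as follows", with 9 + 2 primary care and 6 + 1 mental health clinics, that is 15 + 3 = 18.

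Section {20c} keeps every randomised participant in the primary analysis and carries the last value forward, so someone seen only at baseline keeps their baseline smoking status.

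**The concern.** Clinics are the unit of randomisation, so the precision of the comparison is limited by the arm with the fewest clinics. A normal quantile with the between-clinic variance treated as known takes no account of estimating the TAU rate from three clinics. The stated power may therefore belong to a test that does not hold its nominal 5%.

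A power of 99.4% means a type II error of 0.6% at the planned effect. If the real figure is several times larger, readers will give a null result more weight than the design supports. The number of TAU clinics is the input that matters most here, and the article gives it as both two and three.

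**Working it through.** **Inputs.** From Sample size {14}: rates 0.25 and 0.05, ICC 0.05, two-sided 5%, 1000 smokers in 14 clinics and 200 in 3, 50% dropout (500 and 100 remain). Two assumptions are not in the documents: equal clinic sizes and beta-binomial clustering.

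**1. The plan's own figure.** Design effect = 1 + (m − 1) × 0.05, with m = participants per clinic. Power = Φ(0.20/SE − 1.96), with unpooled SE = √(0.1875/n₁ + 0.0475/n₂) and n the effective sizes.

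- After dropout: m = 35.7 and 33.3; design effects 2.74 and 2.62; effective n 182.8 and 38.2; SE 0.0476; power **98.7%**.
- No dropout: design effects 4.52 and 4.28; effective n 221 and 46.7; SE 0.0432; power **99.6%**.
- With a pooled-null variance instead: 88.2% after dropout, 94.7% without.

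So 99.4% needs the unpooled form. It lies between the two unpooled values, above the one that uses the stated dropout.

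**2. Does that test hold 5%?** Simulated rejection rates of the unpooled z-test under the null, 15+3 clinics, 500 v 100, ICC fixed at its true 0.05:

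- 10.0% at a common rate of 0.05
- 6.9% at 0.15
- 6.3% at 0.217 and at 0.25

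If the variance is instead estimated from the clinics and a normal quantile kept, the rates are about 14–16%. Under 25% v 5% the unpooled z-test itself rejects in 95.4% of simulated trials at 15+3, against 98.9% by formula. The pooled-null z-test holds its level (4.2–5.0%) if the ICC really is 0.05, but its simulated power is 89.7%.

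**3. Tests suited to few clusters.** Cluster-level t-tests with (clinics − 2) df, 100,000 simulated trials each, and permutation tests on raw clinic proportions, 4,000 each. Power in %:

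| Analysed | Clinics | Raw t | Arcsine t | Empirical-logit t | Permutation |
|---|---|---|---|---|---|
| 500 v 100 | 14+3 | 83.1 | 89.8 | 92.5 | 83.8 |
| 500 v 100 | 15+3 | 83.1 | 89.9 | 92.7 | 81.3 |
| 500 v 100 | 15+2 | 62.7 | 79.8 | 86.2 | 59.9 |
| 1000 v 200 | 14+3 | 90.4 | 94.8 | 96.5 | – |
| 1000 v 200 | 15+3 | 90.7 | 95.0 | 96.7 | – |

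With three TAU clinics and 500 v 100, the three t-tests had simulated type I error of 4.5–5.2% at the common rates tried. The 15+3 permutation figure is stratified by department (55 × 7 = 385 allocations), with type I error 4.8%.

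**4. Clinic counts.** Going from 14 to 15 intervention clinics moves the z-formula from 98.7% to 98.9% and leaves the raw t-test at 83.1%. Going from three TAU clinics to two moves the z-formula only to 97.4%, but takes the raw t-test to about 63%. The stated 5:1 ratio fits 15:3; 14:3 is 4.7:1 and 15:2 is 7.5:1.

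**5. Who the 25% and 5% describe.** If they are rates among all enrolled, the 1000 v 200 rows apply. If they are completers' rates and every dropout carries smoking forward (an assumption, and the extreme case), the analysed rates become 0.5 × 25% = 12.5% and 0.5 × 5% = 2.5%. With 14+3 clinics the raw t-test then has 49% power and the logit t-test 80%. Sample size {14} does not say which reading is meant.

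**The case against.** The section openly names a large-sample method, and its unpooled form gives 98.7% or 99.6% depending on dropout. A reader might infer an arithmetic error; that does not stand. The 88.2% from a pooled-null variance does not prove one either, because the section does not specify that form.

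A reader might also infer that any valid test has only 80–85% power. That range belongs to tests on raw clinic proportions. Arcsine and logit t-tests hold about 5% too and reach about 90–93%. The logit scale is not foreign to this plan, since section {20a} names a logistic regression that takes account of clustering, though as a sensitivity analysis to a simple comparison.

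The carry-forward rule in {20c} means all 1200 may be analysed, which would make the no-dropout inputs the relevant ones. This stands as a possibility, and it is why a second range is given.

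Finally, two TAU clinics is probably a slip. The sentence in {9} does not add up to eighteen, while {14} and {16a} both say three. The 63% should not be read as the trial's power.

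None of these points restores 99.4%: every small-cluster result above is below it.

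**Conclusion.** The stated power is too high because the approximation behind it does not suit three control clinics. With three TAU clinics and 500 v 100 completers, tests that hold about 5% have roughly 81–93% power: raw t or permutation 81–84%, arcsine about 90–91%, empirical logit about 92–93%. That is a type II error of about 7–19% instead of 0.6%. If all 1200 are analysed and 25% v 5% are the intention-to-treat rates, power is about 90–97%.

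These figures rest on equal clinic sizes (unequal sizes would normally lower them), beta-binomial clustering and an ICC of 0.05. The raw t-test at 14+3 and 500 v 100 ranges from 97% at ICC 0.02 to 58% at 0.10.

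The clinic counts contradict one another and need reconciling. The 14 v 15 difference hardly matters for power; the two v three TAU difference does. It would go too far to call the trial underpowered: on the protocol's inputs, with three TAU clinics and 25% v 5% holding among those analysed, power stays above 80%. Nor does the article claim that a null result would be conclusive; that is a risk in how readers would use the figure.

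**What to change.** Four changes to the text:

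1. Use one clinic count throughout: 15+3 if Sequence generation {16a} describes the actual randomisation. Correct Sample size {14} and Study setting {9} to match.
2. State whether 25% and 5% are rates among completers or among all enrolled under the carry-forward rule in {20c}.
3. Name the small-cluster test for which power is claimed, such as a cluster-level t-test on a stated scale, or a permutation test stratified by department.
4. Replace 99.4% with the power of that test on those inputs, or with the ranges above and their assumptions.

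The sample size need not change. The only cost is a less favourable stated power; no participants are added.

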### Recruitment {15}

All patients currently enrolled at LACDHS and LACDMH sites who meet inclusion criteria are eligible to participate. Participants will be recruited by healthcare providers and staff at LACDHS and LACDMH. An invitation to participate in the study will be offered by LACDHS and LACDMH healthcare providers to all LACDHS and LACDMH enrolled clients, regardless of concurrent medical or mental health issues, through initial evaluations at intake appointments and through regular healthcare appointments with existing clients. To assist with reaching the target sample size, recruitment efforts will extend to individuals on Medi-Cal, My Healthy Way LA beneficiaries, and individuals without insurance coverage. LACDHS and LACDMH healthcare providers will refer patients interested in the study to the research staff located at that site. Furthermore, healthcare providers will invite potential study participants through flyers, video presentations, and distribution of study referral information. Enrolled LACDHS and LACDMH clients can also self-refer at any time and do not need to be referred by their healthcare provider. LACDHS and LACDMH healthcare providers will refer interested smokers to the research team through the LACDHS and LACDMH electronic records, by telephone or email. Following the telephone screening, research coordinators will invite those meeting inclusion criteria to sign an informed consent and to enroll in the study, streamlining recruitment efforts.

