### Concealment mechanism {16b}

There is no concealment.

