### Implementation {16c}

Statistician [name], will perform the randomization at a clinic level using a computer program. The study is a cluster-randomized design protocol. Individual clinics will be assigned to the intervention and TAU on a 5:1 ratio. Study participants empanelled or otherwise being treated by clinicians at TAU clinics are therefore considered to be in the TAU arm, and study participants who receive care from intervention sites are in the intervention arm. Clinic staff and study coordinators will notify clinics of their assignments. Following the eligibility check and informed consent, the research team will enroll participants into either clinics that provide smoking cessation services or TAU clinics. The sites will be identified by a rotating code, so participants cannot learn which sites are TAU.

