## Assignment of interventions: blinding

### Who will be blinded {17a}

There is no blinding.

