## Statistical methods

### Statistical methods for primary and secondary outcomes {20a}

Final analyses will begin in year 4 at quarters 2 and 3. Data analysis will utilize an intention-to-treat (ITT) approach as the primary analysis. An additional set of analyses will use a per-protocol (PP) paradigm that will only use subjects who attend at least 3, out of four visits, including month 12. Descriptive statistics will include number, percent, and mode for categorical data (gender, race/ethnicity, site, LACDHS/LACDMH, number of visits). Continuous variables of clinical characteristics (number of cigarettes smoked, number of years smoked, Fagerstrom score) and Behavioral Measures Battery will be used to describe the study population. Non-normal distribution will be transformed to satisfy the normality assumption for the parametric statistical tests. Scale variables will be presented as min, max, and median. Graphical presentations (histograms, boxplots, and spaghetti plots) will be used to facilitate the visualization of data and the time trend of endpoints and baseline variables. All statistical analyses will be performed using SAS 9.2 and a *P*-value <0.05 will be considered statistically significant.

For model 1, we will perform an analysis of covariance with the baseline value (site, racial-ethnic group, number of visits, age, weight, smoking status, and survey scores) as the covariate and compare the value at the end of the study. To evaluate the change over time between the groups that incorporates all the measures collected over the timeframe of the study, then a two-way repeated measures analysis of variance model will be used. For model 2, a multiple logistic regression model would be built using independent variables such as treatment group and pre-determined baseline covariates (including study site). We posit that using a covariate-adjusted model to evaluate outcome provides a sensitivity analysis for the primary results of a simple comparison of the achievement of smoking cessation. For both models, the analyses will incorporate the cluster-randomized design into the model using an appropriately chosen variance-covariance structure (up to the use of an unspecified structure). In addition, the models will include a term for LACDHS versus LACDMH sites and their interaction with the intervention group.

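### Staff who know their clinic's arm refer participants after services start, yet the primary cessation result is unadjusted and the adjusted model behind it is misspecified

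*Protocol article*

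**What the plan says.** All places are in the protocol article.

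- **Order of events.** Participant timeline {13} says the study "begins with implementation and delivery of the smoking cessation services, followed by healthcare staff surveys, study participant recruitment by the healthcare staff".
- **Who recruits.** Recruitment {15}: "Participants will be recruited by healthcare providers and staff at LACDHS and LACDMH". Patients may also refer themselves. Research coordinators then screen by telephone and enrol.
- **Who knows the arm.** Concealment mechanism {16b}: "There is no concealment". Who will be blinded {17a}: "There is no blinding". Implementation {16c}: "Clinic staff and study coordinators will notify clinics of their assignments".
- **Unit and number.** Sequence generation {16a} allocates clinics, "with three TAU sites and fifteen intervention sites", split by department.
- **Analysis hierarchy.** Statistical methods {20a} describes the covariate-adjusted model as "a sensitivity analysis for the primary results of a simple comparison of the achievement of smoking cessation". Model 2 (logistic) counts study site among its baseline covariates. Model 1 (analysis of covariance) lists site and number of visits as baseline values. Both models are to reflect the clustering and to carry a department term with its interaction with arm.

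**The concern.** Randomising clinics balances, in expectation, the populations that the clinics serve. It does not balance the people who enter the study if they are identified afterwards by staff who know what their clinic offers. An intervention clinic can offer counselling groups and medication management. A TAU clinic has helpline information and usual counselling. The patients whom staff put forward, and those who come forward themselves, can therefore differ in readiness to quit, which plausibly predicts the outcome.

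A cluster correction does not help here: it widens the standard error but leaves the estimate where it is. Adjustment for baseline predictors can remove the measured part of such a difference. The plan reserves adjustment for a secondary role and specifies it in a form that does not work cleanly. At stake is whether a modest observed difference in quitting can be read as an effect of the services.

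**Working it through.** **1. Does the mitigating text hide the arm from those who refer?**

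- *Invitation of all enrolled clients* (Recruitment {15}). This equalises the offer if it is followed. Interest, referral and consent come after it and are open to influence.
- *Shared criterion of having thought about stopping smoking* (Eligibility criteria {10}). This narrows the spread in motivation in both arms, but readiness can still vary among those who meet it.
- *Rotating site code* (Implementation {16c}). It is aimed at participants. The same section has the clinics told their assignment.
- *Screening by research coordinators* (Recruitment {15}). They see only people already referred or self-referred, and nobody is blinded.

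None of the four conceals the arm from the referring staff.

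**2. Is the adjusted model usable as written?**

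- *Study site.* Each of the 18 clinics is wholly in one arm. With fixed effects for 18 clinics, the arm indicator is the sum of the 15 intervention-clinic indicators, so arm and site cannot be estimated together. Site cannot be read as department, because department is a separate term.
- *Number of visits.* It accrues over the 12 months after enrolment and may itself respond to arm, so conditioning on it can distort the arm contrast.

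**3. The plan's own figures.** Sample size {14} assumes 25% versus 5% abstinence, a difference of 20 points, with 1000 and 200 enrolled in 14 and 3 clinics, 50% dropout and an ICC of 0.05.

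- Intervention: 500/14 = 35.7 per clinic; design effect 1 + 34.7 × 0.05 = 2.74; effective n 182.8.
- TAU: 100/3 = 33.3 per clinic; design effect 1 + 32.3 × 0.05 = 2.62; effective n 38.2.
- Standard error (unpooled): √(0.25 × 0.75/182.8 + 0.05 × 0.95/38.2) = 0.0476.
- Power: Φ(0.20/0.0476 − 1.96) = 98.7%. Without dropout it is 99.6%. The stated 99.4% lies between.

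This figure concerns sampling error only and says nothing about selection.

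**4. Illustration of size.** The documents give no selection figures, so these inputs are assumptions: no service effect, motivated smokers quit three times as often as others, and the motivated share is s₁ = 70% in intervention and s₀ = 40 to 50% in TAU. Only the 5% TAU quit rate comes from the plan. With q the quit rate in less motivated smokers:

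- q(1 − s₀) + 3q·s₀ = 0.05, so q = 0.05/(1 + 2s₀).
- False difference = 2q(s₁ − s₀).

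| s₀ | q | 3q | False difference | Intervention rate | Risk ratio |
|---|---|---|---|---|---|
| 50% | 2.50% | 7.50% | 0.05 × 0.20 = 1.0 point | 6.0% | 1.20 |
| 40% | 2.78% | 8.33% | 0.0556 × 0.30 = 1.7 points | 6.7% | 1.33 |

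These are 5% (1.0/20) and 8% (1.7/20) of the planned difference. Even if every intervention enrollee were motivated, the gap would be 7.5 − 5 = 2.5 or 8.3 − 5 = 3.3 points.

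**5. How much information the TAU arm carries.** At 5% quitting, TAU yields 0.05 × 100 = 5 quitters if the rate applies to completers, or 0.05 × 200 = 10 if it applies to all enrolled, spread over three clinics.

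**The case against.** The strongest reply is that a simple primary comparison with an adjusted sensitivity analysis is a common and defensible choice. The plan already contains adjusted, cluster-aware models, so a divergence between simple and adjusted results would be visible. Selective referral probably works mostly through willingness that no questionnaire captures, so changing which analysis is primary cannot cure it. A model with many covariates would be fragile with 5 to 10 TAU quitters, and its odds ratio would no longer be the difference in proportions used for the power calculation.

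Much of this stands. It limits the point to which analysis leads and how it is specified, and it shapes the repair: few covariates, a small-sample correction and a risk-difference scale. It does not remove the point. The analysis meant to reveal selection is the one that is misspecified, and a headline result that makes no allowance for measured differences is a weak choice when recruiters know the arm.

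A reader might go further and infer that selective referral took place, or that it could by itself produce the effect the trial is powered for. The documents support neither. They show an opportunity, not an occurrence. Larger illustrations need rates that do not fit the plan: quit rates of 25% and 5% with motivated shares of 90% and 30% give 0.20 × 0.60 = 12 points, but imply TAU quitting of 0.30 × 25 + 0.70 × 5 = 11%, more than twice the planned 5%.

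**Conclusion.** The point holds in limited form. Recruitment by staff who know the arm, after services have begun, leaves the comparison open to differences in who enrols. The plan's primary analysis does nothing about the measured part of those differences, and the adjusted models cannot be fitted or interpreted cleanly as listed. That the primary comparison is unadjusted is inferred from its contrast with the covariate-adjusted model, and the wording leaves little room for another reading.

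The size of any bias cannot be derived from the documents. On the assumptions shown it is about 1 to 2 points, a risk ratio of 1.20 to 1.33 with no service effect. That could not account for a 20-point difference. It would matter if the observed difference were small: for an observed gap of, say, 5 points, it would be 20% to 33% of it (1.0/5 and 1.67/5).

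**What to change.** In Statistical methods {20a}:

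- Make the primary analysis a cluster-aware logistic model of cessation on arm, department and a short pre-specified set of baseline predictors already collected, for example cigarettes per day, FTND and WI-PREPARE.
- Enter clinic as the cluster term, with a small-sample correction suited to three TAU clinics.
- Report the result as a standardised risk difference, so that it stays on the scale of the power calculation.
- Remove study site as a fixed covariate and number of visits from both models.
- Keep the simple comparison as the sensitivity analysis.
- State as a limitation that unmeasured selection through referral and self-referral remains.

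The cost is a change of wording, with no new data collection. The price is a primary estimate that depends on a model fitted with few TAU quitters, which is why the covariate list must stay short. Recruitment began in October 2019, so the recruitment process itself cannot be redone. The change should be fixed before the final analysis. Because the planned interim analysis counts subjects who have stopped smoking, the amendment should say whether those counts had been seen by arm.
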